## Abstract

**Background:**

Migraine is a highly prevalent disease and the leading cause of years lived with disability in women. The development of therapies targeting the calcitonin gene-related peptide (CGRP) pathway has provided the first mechanism-based approach for migraine prevention. Although these treatments have demonstrated substantial efficacy, 30–50% of patients do not achieve an adequate clinical response. This variability underscores the need of prospectively identifying responders and non-responders, thereby enabling precise treatment allocation and improving clinical outcomes.

**Objectives:**

BIOMIGA is a multicentre phase IV study aimed at identifying biomarkers of response to anti-CGRP therapy in migraine through integrated clinical, molecular, genetic, and neuroimaging profiling, with patients stratified according to treatment response after 3 months treatment cycle with an mAB targeting the CGRP receptor (erenumab).

**Methods:**

Individuals with episodic and chronic migraine eligible for treatment with erenumab are enrolled along with healthy control subjects. Biomarkers are collected longitudinally at baseline and at the end of a 3-month treatment with erenumab. Circulating levels of CGRP and cytokines, genetic polymorphisms, and DNA methylation are assessed. Advanced structural and functional MRI scans are performed simultaneously, and comprehensive psychometric scales are used to map central pain processing and clinical burden. The final multimodal dataset is analysed using machine learning to develop and evaluate integrated models of treatment response.

**Expected results:**

The integration of multimodal data from patients and healthy controls, stratified according to treatment response, will enable the identification of a panel of biomarkers predictive of response to anti-CGRP therapy.

**Conclusion:**

The BIOMIGA trial represents a major step forward in the management of migraine. By combining a comprehensive multimodal profiling with a real-world, multicentre cohort of patients treated with erenumab, the study provides a framework for identifying robust biomarkers of treatment response and lays the foundation for truly individualised migraine prevention strategies.

**Clinical trial registration:**

ClinicalTrials.gov, identifier NCT04503083.

## Background

Migraine is a complex and highly prevalent neurological disorder (1) characterised by the abnormal processing of internal and external stimuli with recurrent activation of the trigeminovascular system. The release of vasoactive neuropeptides, particularly calcitonin gene-related peptide (CGRP), from trigeminal afferents in the meninges, promotes vasodilation, sterile neurogenic inflammation, and central sensitisation in brainstem and thalamic networks (2). These mechanistics insights have led to the development of preventive and acute treatments that selectively target the CGRP pathway, including monoclonal antibodies (mABs) against CGRP or its receptor and the small-molecule CGRP receptor antagonists (gepants).

CGRP-targeting mABs are large molecules with limited penetration across the blood–brain barrier, minimal pharmacokinetic interactions and long half-life. Because of these characteristics, CGRP-targeting mABs are administered parenterally monthly or quarterly and ensure high adherence to treatment randomized controlled trials (RCTs) long-term extension studies (OLEs) and real-world (RWE) cohorts confirm sustained reduction in monthly migraine days,(MMDs) disability, and acute medication use, with favourable tolerability profiles in both episodic (EM) and chronic migraine (CM), including patients who have previously failed multiple preventive treatments (3–6). In light of the robust and high-quality evidence supporting their efficacy and safety (4), mABs targeting CGRP or its receptor should be considered a first-line preventive treatment for migraine (7). This position has been endorsed by several international and national scientific societies. However, implementation remains limited in many settings due to heterogeneous reimbursement policies, despite pharmacoeconomic evaluations consistently indicating that CGRP-targeting mABs and, in certain contexts, gepants are cost-effective for CM, particularly when considering indirect costs and productivity gains (8–10). In this context, identifying predictors of differential treatment response is crucial to inform equitable and evidence-based reimbursement strategies, ensuring appropriate patient selection while aligning clinical practice with current scientific recommendations.

However, only a subset of patients achieve a ≥ 50% or ≥75% reduction in migraine days with CGRP-pathway-targeted therapies, highlighting the need for precision medicine approaches capable of matching individuals to the most effective therapy (11). Central to such approaches is the identification of robust biomarkers that can predict the likelihood of response. Despite decades of investigation, no biomarker has yet been validated for routine clinical use in migraine, either for diagnosis, disease staging, or prediction of treatment response (12, 13).

Multiple classes of candidate biomarkers have been explored. Circulating peptide markers, including CGRP and related neuropeptides, show increases during spontaneous and induced attacks and correlate with headache frequency and acute medication intake, but inter-individual variability, methodological differences and overlapping values with controls have limited their clinical utility (14, 15). Peripheral microRNAs show changes in chronic migraine and medication overuse and may normalise after detoxification or anti CGRP preventative therapy, but findings remain inconsistent and based on small samples (16, 17). Integrated molecular models combining miRNA profiles and genetic risk score have recently shown high discriminative accuracy, supporting multi-omic approaches, but still lack proper accessibility (18). Neuroimaging studies have shown structural and functional changes in pain-processing networks. Multimodal MRI can differentiate between migraine patients and controls, although there are currently no reliable imaging predictors for predicting response to CGRP-targeted treatments (13, 19, 20). Single-nucleotide polymorphisms (SNPs) modestly contribute to the risk of migraines, while changes in methylation at CGRP-related loci may affect migraine chronicity and the response to treatment (21–23). Genome-wide methylation studies further support distinct epigenetic signatures in migraine, but their relationship with pharmacological response is still largely unexplored.

This persistent gap in the identification of a single biomarker likely reflects the complex and dynamic nature of migraine biology – with distinct attack, pre−/post-dromal and interictal phases – the multiplicity of implicated mediators CGRP, PACAP38 and other neuropeptides, monoamines, inflammatory pathways, miRNAs, etc., and the involvement of both peripheral and central structures, together with marked interindividual variability of clinical expression (24). Methodological heterogeneity across studies – including differences in sampling paradigms, assay techniques, patient populations and outcome definitions – has further contributed to inconsistent findings and limited precision of biomarker estimates (15).

The advent of migraine-specific preventive therapies targeting the CGRP pathway offers an unprecedented opportunity to stratify patients according to response to a well-defined molecular mechanism and to link biomarkers to a precise pharmacological target (11). In parallel, advances in high-throughput and systems biology approaches allow the integration of multi-omic signatures with deep clinical phenotyping, neuroimaging and digital biomarkers, while sophisticated animal models continue to refine mechanistic understanding of CGRP-related neuroinflammation (24, 25). Recent work indicates that artificial intelligence and machine-learning methods can extract predictive patterns of response to anti-CGRP mABs from large, heterogeneous datasets, although current models remain preliminary, require external validation and are not yet applicable in clinical practice (26–29).

The biomarkers selected for the BIOMIGA study reflect a unified pathophysiological rationale, and each domain detects a complementary level of CGRP-mediated trigeminal-vascular activation. Peripheral neuroinflammatory signalling is associated with circulating levels of CGRP and cytokines, which reflect the degree of trigeminal activation at the time of treatment. Individual biological susceptibility to dysregulation of CGRP signalling is assessed through genetic variants and DNA methylation profiles at loci within the CGRP pathway. Central network reorganisation, a downstream consequence of prolonged trigeminal-vascular input, is quantified through resting-state functional connectivity. Together, these converging signals at all levels, rather than a single marker, are expected to predict response to erenumab. The resulting predictive models is expected to guide treatment decisions in patients with severe disability, such as those with CM, and provide essential evidence to healthcare systems and payers to support the rational and equitable allocation of advanced therapies.

We therefore hypothesise that the assessment of a wide panel of migraine-relevant features will yield a composite biomarker profile capable of predicting the response to treatment with anti-CGRP mABs in migraine prevention.

To address this hypothesis, BIOMIGA (BIOmarkers of MIGraine) project (Figure 1) was designed as a proof-of-concept multidisciplinary study with the following specific objectives:To define the clinical and omics differences between subjects with migraine stratified according to their response (responders vs. non-responders) to treatment with a CGRP-targeting mAb;To identify a predictive profile using advanced machine learning techniques to analyze the integrated clinical and omics database generated from responder and non-responder data;To integrate the findings from human studies with the evaluation of CGRP-targeting drugs in validated animal models of migraine.

**Figure 1 fig1:**
[figure not shown]
BIOMIGA logo: A multidisciplinary approach to the identification of biomarkers of migraine: A proof-of-concept study based on the stratification of responders to CGRP-targeting monoclonal antibodies.

In this manuscript, we will illustrate the BIOMIGA protocol that was devised to achieve objectives 1 and 2.

## Aim

Our primary working hypothesis is that patients with high-frequency episodic migraine (32) (HFEM) or CM who respond to treatment with a CGRP-targeting mAb (erenumab) exhibit a distinct clinico-omic profile compared with non-responders.

For this purpose, we will analyse a large set of variables collected from a cohort of subjects with HFEM or CM exposed to a 3-month cycle of migraine preventive treatment with a CGRP-targeting mAb. The large multimodal dataset will be analysed will be analysed with advanced multivariable modelling, including machine-learning and deep-learning techniques for feature selection, model building and internal validation. This process will identify distinct profiles associated with the responder or non-responder status, therefore providing the foreground to support personalised, cost-effective preventive treatment strategies in HFEM and CM.

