#### Descriptive and inferential statistics

All computations were conducted via *R* software (version 4.4.0). Quantitative variables were compared using the cross-sectional Mann–Whitney test, whereas categorical variables were assessed via the chi-square test or Fisher’s exact test. A value of *p* < 0.05 was considered statistically significant. The statistical plan included baseline comparisons between R and NR across clinical, anamnestic, psychological, and disability measures. Variables were also compared between healthy controls and migraine patients, stratified for gender and diagnosis. Predictive thresholds for circulating serum *α*-CGRP, IL-1β, and TNF-α levels were estimated in patients using binomial logistic regression (generalised linear model, GLM).

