#### Mitigation of confounding factors

Given the real-world observational design of the BIOMIGA study, several measures were adopted to minimise the influence of potential confounding factors. Clinical outcome classification were based on prospectively collected headache diaries, which represent the reference standard for the assessment of migraine outcomes in real-world studies and reduce recall bias through systematic longitudinal recording of headache frequency and acute medication use (39). Standardised eligibility criteria limited major sources of confounding, including medication overuse headache, concomitant preventive treatments, severe neurological or psychiatric disorders, cardiovascular diseases, substance abuse, and other medical conditions potentially affecting biomarker levels or treatment response.

Demographic and clinical variables, including age, sex, migraine subtype, disease duration, baseline monthly migraine days, disability measures, acute medication intake, and relevant comorbidities, were systematically collected and evaluated as potential confounders. Analyses aimed at identifying clinically meaningful cut-offs for circulating CGRP concentrations were performed using GLM for prespecified clinical and demographic covariates to estimate independent associations while accounting for potential confounding. For epigenetic analyses, standardised procedures were adopted to minimise pre-analytical variability. Quality-control procedures and batch-effect correction methods were applied where appropriate, and known determinants of DNA methylation variability, including age, sex, medication exposure, and lifestyle-related factors such as smoking habits, were considered during statistical analyses to reduce potential confounding.

To reduce variability in neuroimaging-derived measures, MRI data were acquired using standardised acquisition protocols and processed through harmonised quality-control and preprocessing pipelines. Structural and functional MRI datasets underwent visual and automated quality assessment, with exclusion of scans affected by major artefacts or excessive motion.

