Established preprocessing procedures, including motion correction, spatial normalisation, and nuisance signal regression for functional MRI data, were applied to minimise non-biological sources of variability. In addition, demographic and imaging-related factors known to influence brain measures, such as age, sex, and head motion parameters, are going to be considered during statistical modelling and feature selection procedures.

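### Migraine subtype is listed as a potential confounder but is not carried into the stated responder v non-responder analyses, so a marker of chronicity could appear as a marker of response

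*Protocol article*

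**What the plan says.** The Aim section sets the main contrast in a pooled population: "patients with high-frequency episodic migraine (32) (HFEM) or CM who respond to treatment with a CGRP-targeting mAb (erenumab) exhibit a distinct clinico-omic profile". Under Eligibility criteria, HFEM means 8–14 monthly headache days and CM means 15 or more, with more than 25 excluded.

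Descriptive and inferential statistics names the tests: "Quantitative variables were compared using the cross-sectional Mann–Whitney test", and chi-square or Fisher for categorical variables. It then says "The statistical plan included baseline comparisons between R and NR across clinical, anamnestic, psychological, and disability measures", with no stratum or covariate. Diagnosis appears in the next sentence, which concerns a different comparison: "Variables were also compared between healthy controls and migraine patients, stratified for gender and diagnosis".

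Mitigation of confounding factors recognises the issue. "Demographic and clinical variables, including age, sex, migraine subtype, disease duration, baseline monthly migraine days" and other items "were systematically collected and evaluated as potential confounders". The only analysis there that is said to use clinical covariates is the model for CGRP cut-offs, and the text does not say whether subtype is one of them. For methylation the named factors are age, sex, medication exposure and lifestyle. For imaging they are scanner site (Acquisition protocol) and factors "such as age, sex, and head motion parameters". The screen under Preprocessing and feature selection tests each candidate marginally against response category.

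**The concern.** The Background section itself links the candidate markers to chronicity. It reports that circulating CGRP correlates with headache frequency, and that "changes in methylation at CGRP-related loci may affect migraine chronicity and the response to treatment". The rationale also treats central network reorganisation as a result of prolonged trigeminovascular input. Three marker domains may therefore differ between HFEM and CM whether or not they say anything about erenumab.

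If the chance of a 50% reduction also differs by diagnosis, responders and non-responders will hold different mixes of HFEM and CM. A pooled test then picks up any variable that separates the two diagnoses. The study could offer as a candidate response biomarker something that restates a diagnosis the clinician already has. The reverse loss is possible too: where diagnosis explains marker variance but not response, the pooled test is less sensitive than a stratified one.

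**Working it through.** **Inputs from the document.** 168 migraine patients, 6% loss, 30% in each extreme response group (Sample size calculation). Evaluable: 168 × 0.94 = 157.9, taken as 158. Per extreme group: 168 × 0.30 × 0.94 = 47.4, which agrees with the stated 47.

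**Inputs assumed, because the document gives none.** CM share p; response rates r_H (HFEM) and r_C (CM); a marker that is higher in CM by d SD and unrelated to response within each diagnosis.

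**Formula.** With overall response rate r = (1−p)r_H + p·r_C, the CM share is a = p·r_C/r among responders and b = p(1−r_C)/(1−r) among non-responders. Pooling creates a spurious difference of d(b−a). Its standard error is √{[1 + d²a(1−a)]/n_R + [1 + d²b(1−b)]/n_NR}. With z the ratio of the two, the false-positive rate is about P(Z > 1.96 − z) + P(Z < −1.96 − z).

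**Worked case: p = 0.5, 60% v 30%, d = 0.8.** r = 0.45, so n_R = 71.1 and n_NR = 86.9; a = 0.333, b = 0.636. Spurious difference 0.8 × 0.303 = 0.242; standard error 0.171; z = 1.42; false-positive rate 29%. Simulated Mann–Whitney: 30%.

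**R v NR, N = 158, 50:50 split, d = 0.8**

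| Response HFEM v CM | b − a | Formula | Simulated, pooled | Simulated, stratified |
|---|---|---|---|---|
| 50% v 50% | 0 | 5% | 4% | 4% |
| 50% v 40% | 0.101 | 8% | 9% | 6% |
| 55% v 35% | 0.202 | 16% | 17% | 5% |
| 60% v 30% | 0.303 | 29% | 30% | 5% |

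The stratified column is the van Elteren test, with 2,000 runs per setting. Over d = 0.3 to 0.8 and CM shares of 50% to 70%, the pooled rates are about 5–9% (50% v 40%), 6–17% (55% v 35%) and 9–30% (60% v 30%). The most extreme setting examined, 65% v 35% with d = 1.2, gives z = 0.36/0.183 = 1.96 and about 50%.

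**Super-responders v full non-responders, 47 per group.** Assume two thirds HFEM in one group and one third in the other, so b − a = 1/3. For d = 0.8: difference 0.267, standard error √(2 × 1.142/47) = 0.220, z = 1.21, rate 23% (simulated 21–22%). For d = 0.5 and 1.2 the formula gives 12% and 39%. This concerns a difference in marker level at one time point.

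**Power, true effect 0.45 SD, response unrelated to diagnosis.** With d = 0.8: about 70% pooled v 77% stratified. With d = 0: 78.0% v 77.2%.

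**The case against.** **The plan is not silent on diagnosis.** A reader might infer that it contains no stratification or adjustment for diagnosis at all. The text does not support that. Subtype is listed as an evaluated confounder, the CGRP cut-off analysis uses clinical and demographic covariates, and the control comparison is stratified by diagnosis. The methylation and imaging lists are introduced as examples, so they may not be complete, and the article defers downstream methylation analysis and imaging processing to later publications.

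**The primary analysis gives some protection.** The random-forest models start from clinical and biochemical variables and add genetic, epigenetic and MRI features in steps. If diagnosis or headache frequency is in the first block, a later feature that only stands in for chronicity should add little. For prediction, diagnosis is also a legitimate predictor. This stands in part. It does not condition the univariate tests, the screen or the importance rankings on diagnosis, and CGRP sits in the same first block as the clinical variables.

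**The R v NR sentence covers clinical measures.** That is correct: it names clinical, anamnestic, psychological and disability measures. The omics and imaging R v NR comparisons are announced under Efficacy endpoint analyses, which names neither a test nor an adjustment. It would be too much to say that those comparisons are fixed as unadjusted.

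**Chronicity may be a mediator.** The Background wording allows methylation to act on chronicity and through it on response. Stratifying could then remove real signal. This stands, and it is why the unadjusted result should not be relegated.

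**Size and consequence.** The error rates are assumed, and near nominal at 50% v 40%. The longitudinal imaging contrasts concern change from baseline, where a stable difference between diagnoses largely cancels, so the figures for marker level do not carry over to them. The machine-learning work is labelled exploratory. All of this limits the weight of the point. It does not explain why a confounder that the authors list is absent from the tests they name.

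**Conclusion.** The point holds as a gap between two parts of the plan. Subtype and baseline migraine days are recognised as potential confounders, but the stated R v NR tests, the named methylation and imaging factors and the feature screen do not use them.

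The possible effect runs from none, if response rates are equal in HFEM and CM, to a false-positive rate of about 30% for a large gap in response with a 0.8 SD marker shift, and to about 50% at the extreme. A stratified test holds about 4–6% throughout. These figures show what could happen under stated assumptions; they do not estimate the bias in this trial, because the document gives no diagnosis split, no response rates by diagnosis and no marker shift.

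Two stronger readings should be resisted: that diagnosis is ignored altogether, and that the unadjusted contrast is invalid. The first conflicts with the text. The second assumes that chronicity is purely a confounder, which the Background does not establish.

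**What to change.** - In Efficacy endpoint analyses and Descriptive and inferential statistics, report each baseline R v NR and super-responder v full non-responder comparison stratified by diagnosis: van Elteren for quantitative variables and Cochran–Mantel–Haenszel for categorical ones. Keep the unadjusted result beside it.
- Name diagnosis, or baseline headache days, as a covariate in the methylation and imaging group models.
- State an interpretation rule: a marker is described as associated with response beyond diagnosis only if the association persists in the stratified or adjusted analysis. Passing the marginal feature screen is not enough for that wording.

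Cost: wording, a little code and one more column of results. Diagnosis is confirmed for every patient at visit 2, and Status of the study says that processing for the stratified groups is still under way. If diagnosis is unrelated to the marker, the loss of power is under about one percentage point (78.0% v 77.2% above).
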